## Relevance

This study concerns the validation and evaluation of a prioritized early detection instrument that will be completed by parents of preschool children, discussed with the Youth Health Care professionals (generally specialized Youth Health Care nurses and specially trained physicians), enabling shared decisions with parents concerning the well being of their child and family. This proposal therefore connects to the main aim of the ZonMw program Care for Youth.

This proposal specifically fits into Priority [A] of the recently established ZonMw program Care for Youth (Zorg voor Jeugd); i.e. 'Drive back (risks for) parenting problems regarding children below age 7 years'. Screening for emotional and behavioral problems by preventive Youth Health Care at child age 24 months using the BITSEA, followed by timely referral and adequate follow-up, may effectively prevent risk full parenting situations, and may effectively improve optimal development of young children.

The BITSEA is recommended by the Dutch Invent-group, but there is little knowledge about the psychometric characteristics in the setting of day-to-day, regular preventive Youth Health Care in the Netherlands. Worldwide there are only very few longitudinal studies with the BITSEA, which are necessary to evaluate the predictive validity of this promising instrument. In this study we will evaluate the impact of screening using the BITSEA at child age 2 years in routine preventive Youth Health Care with a 12 months follow-up, compared to screening using the KIPPI-2, which constitutes 'usual care'. This knowledge will be important for decisions by RIVM Center for Youth Health and other responsible agencies about nationwide implementation of screening for emotional and behavioral problems using the BITSEA at preschool age in preventive Youth Health Care centers, and in the near future centers for Youth and Family.

The study group consists of toddlers 2-3 years old, with a Dutch as well as a non-Dutch background in the varied region of Rotterdam Rijnmond (inner city areas as well as rural areas are represented). The young age of our study population (age 2-3 years), and the high proportion of non-Dutch children in the study (estimated to constitute 25% of the whole study population), connects well to two other priorities in the ZonMw program Care for Youth.

Note: In the city of Rotterdam, about 50% of the 2 year olds are of non-Dutch origin; i.e. circa 10% of Surinam origin, 15% of Turkish origin, 10% of Moroccan origin and 15% of other ethnic minority groups.

Using the BITSEA as a screening tool in the preventive Youth Health Care for preschool children has important implications for the partners in the so called chain-of-care for children and families. Youth Care is a very important partner in this chain, and for this reason plays an important role in future Centers for Youth and Family. The screening tools used by preventive Youth Health Care need to be feasible and proper instruments for the entire chain-of-care. This study will pay attention to these prerequisites.

---

## Study Design

The study consists of two parts. In Part 1, test properties of the BITSEA will be determined in 2-year olds (Research question 1). In Part 2 the use of the BITSEA as screening tool in 2-year olds will be evaluated in comparison with the use of the KIPPPI-‘Consultatie Bureau Signalerings Instrument 2-jarige’, which constitutes ‘usual care’ (Research questions 2-4).

The study will take place in the (broad) Rotterdam Rijnmond area, including the Dordrecht area, Capelle a/d IJssel, the Rotterdam area, and the Schiedam/Vlaardingen area. The GGD Public Health Service Rotterdam Rijnmond participates in the study. The GGD organizes the Youth Health Monitor, which will contain the screening tools for emotional and behavioral problems that parents complete, and bring along to their regular visit to the preventive Youth Health Care (YHC) center when their child is 24 months old. The four practice organizations for preventive Youth Health Care for preschool children in the study area (Ouder- en Kindzorg; Consultatiebureaus) will participate in the study; their professionals (specialized YHC-nurses, in cooperation with specifically trained YHC-physicians) use the screening tools for emotional and behavioral problems, and decide on referral and follow-up care.

In the study, the Child Behavior Checklist 1,5-5 (CBCL 1,5-5) will be used to determine concurrent validity of the BITSEA. Additionally, in the study data of a ‘clinical’ sample will be used to add to the validation of the BITSEA. In Part 2 of the study follow-up measures at age 36 months will be used, including repeated measurements of BITSEA and CBCL 1,5-5 and (medical) chart review and review of a comprehensive registers of care in the Rotterdam Rijnmond area.

Data collection regarding Part 1 and Part 2 of the study overlap.

Please refer to the attached Annex with a schematic overview of study populations and design of Part 1 and Part 2 of the study. Please also refer to the attached Annex with a systematic review of the literature on the BITSEA.

Theoretical model applied in the study:

The theoretical model applied in this study, is the model of screening for abnormalities, followed by referral, diagnosis and early treatment if indicated (see Mackenbach et al, 2008, page 240-253). This model of screening has been developed in the medical setting, e.g. for early detection and treatment of tuberculosis (mid 20th century) or early detection and treatment of specific cancers (late 20th century). Late 20th century, early 21st century this model was transferred to the early detection, referral, diagnosis and treatment of emotional and behavioral problems (and even risks for the development of such problems) in childhood (Hermanns et al, 2005).

The underlying assumption of the model of screening is that early detection, diagnosis and treatment (i.e. earlier than would have happened in the ‘natural course of events’, i.e. without the screening procedure) results in outcomes that are better compared to outcomes in the case of no screening. However, the model of screening acknowledges that depending on the condition for which is being screened, the screening procedure and the setting, a screening procedure may be ineffective or may even be harmful. This is reflected in a quote by Sir Muir Gray ‘all screening programs do harm; some do good as well’ (cited by Mackenbach et al, 2008, page 242). The circumstances that are related to the (potential) outcomes of a screening are summarized in 10 criteria for effective screening that were proposed by Wilson and Jungner (cited by Mackenbach et al, 2008, page 250):

- 
1. The problem/disease should present a public health problem (i.e. a relevant problem at societal level).
  2. An acceptable and effective treatment should be available.
  3. Ample facilities for further diagnosis and treatment should be available.
  4. The problem/disease should have a clear 'latent' phase (i.e. a - hypothetical, ideal - screening test should be helpful to discover a problem/disease that otherwise would have remained unseen/undiagnosed).
  5. The test properties (among which sensitivity, specificity, predictive value of test results) should be adequate.
  6. The screening test should be acceptable for the population.
  7. The natural course of the problem/disease should be known (i.e. the course of the problem/disease in the absence of screening).
  8. Protocols regarding criteria for referral and further diagnosis, and criteria for diagnosis and treatment should be available.
  9. The costs of the whole screening procedure (including referral, diagnosis, and treatment) should be acceptable in the whole context of (health) care.
  10. The screening process should be well-organized and should be embedded in a continuous program (i.e. not an ad-hoc procedure).

Part 1 and Part 2 of this study will clearly contribute to the empirical knowledge needed to decide on future implementation of screening for emotional and behavioral problems in 2-year olds by using the BITSEA in preventive Youth Health Care in the Netherlands, given the 10 criteria of Wilson and Jungner.

Adequate test properties of the BITSEA (criterion 5) have been established in the U.S.. This study will contribute to the knowledge needed to decide on the plausibility of the BITSEA screening in the Netherlands by evaluating the test properties of the BITSEA in the context of day-to-day practice of preventive Youth Health Care in the Netherlands.

Hypotheses applied in Part 2 of the study:

We hypothesize that use of the BITSEA as screening tool compared to KIPPPI-2, results in more appropriate and timely care; and that fewer problems indicated by the CBCL 1,5-5 will be present at 1 year follow-up in the BITSEA group (Intervention condition) compared to the KIPPPI-2 group (Control condition).

We also hypothesize the (relative) costs of the use of the BITSEA to be lower than the costs of the KIPPPI-2 as screening tool.

---

|                                        |
|----------------------------------------|
| PART 1 OF THE STUDY: 'TEST PROPERTIES' |
|----------------------------------------|

In the Part 1 of the study test properties, including psychometric characteristics, sensitivity, specificity and predictive value of the BITSEA will be studied (Research question 1).

Please refer to the attached Annex with a schematic overview of study populations and design of Part 1 and Part 2 of the study. Please also refer to the attached Annex with a systematic review of the literature on the BITSEA, including a description of the instrument. (see Proposal zomnw)

### ***1.1 Design and study population (see annex with overview)***

#### **A. Community sample including parents that visit regular preventive YHC at age 2 years**

A large community sample of 2-year olds (and their parents) in the Rotterdam Rijnmond region with both metropolitan areas with extensive and varied non-Dutch communities and non-metropolitan areas representative of the Dutch population at large, will be used in Part 1 of the study. The study will be carried out by 30 YHC-teams from 4 organizations for preventive YHV in the region. They will obtain informed consent from parents with 2-year olds eligible for the routine health assessment by preventive YHC at age 24 months.

Net 3.000 parents/2-year olds will complete the BITSEA in the course of the study at age 24 months.

Please note that for the purpose of Part 2 of the study (see below) from the total of 30 participating YHC-teams in the study, at random 15 YHC-teams will be assigned to apply the BITSEA as a new screening tool at age 24 months (Intervention condition). The other 15 YHC-teams will apply 'usual care', i.e. application of the KIPPPI-'Consultatie Bureau Signalerings Instrument 2-jarige' (Control condition).

In the Control group in which the KIPPPI-2 is used as a screening tool, the parents will also complete the BITSEA (blinded for the YHC-professionals; in the Control group the YHC-professionals will not use the BITSEA results in the process of health assessment and early detection of emotional and behavioral problems).

In addition to and separately from the Youth Health Monitor, the 3.000 participating parents of 2-year olds in the study will be invited to complete the Child Behavior Checklist 1,5-5 (CBCL 1,5-5), a parent-completed 99-item questionnaire. The CBCL 1,5-5 will be applied to determine the concurrent validity of the BITSEA. The CBCL 1,5-5 is an internationally validated measure that allows making a (provisional) diagnosis respectively problem definition; the CBCL is widely used as gold standard in validation studies (Carter et al, 2004; Achenbach et al, 2000; Reijneveld et al, 2004; Zeijl et al, 2005).

Furthermore, during the regular visit at the YHC center at age 2 years, the YHC-professional will register (routinely) whether emotional or behavioral problems are present, and whether follow-up care or referral is recommended, according to professional judgment based on the protocols (in the Intervention group the BITSEA will be used; in the Control group the KIPPPI-2). Bilingual versions (Dutch; Turkish/Arabic) of the questionnaires will be offered.

---

## B. 'Clinical' sample

Additionally, a 'clinical' sample of net 100 toddlers that are circa 2 years old (18-30 months old) and that have been referred to Youth Care or Youth Mental Health Services will be drawn through Youth Care/Mental Care agencies in the Rotterdam Rijnmond area. Parents of these 2-year olds will also complete the BITSEA, the KIPPI-2, and the CBCL 1,5-5. Given informed consent by the parents, the diagnosis regarding the child will be retrieved from the (medical) chart. Data from the 'clinical' sample will be used to add to the validation of the screening tools.

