### ***1.5 Power considerations***

Since in Part 1 of the study no hypotheses are tested, power calculations are not really applicable. Nevertheless remarks can be made on the precision of the estimates this part of the study will yield.

A sample of 3.100 toddlers (3.000 of the community sample and 100 of the clinical sample) will allow to estimate the area under the Receiver Operating Characteristic (ROC) curve of about 0.90 with a 95% confidence interval of  $\pm 0.02$  (Hanley et al, 1982). A sub-sample size of 217 toddlers (e.g. a specific ethnic sub-group of 7% of the whole population, assuming equal prevalence of emotional and behavioral problems) will allow to estimate the area under the ROC curve of about 0.90 with a 95% confidence interval of  $\pm 0.08$ .

For evaluating concurrent validity of the BITSEA, correlations between specific BITSEA scores and specific, hypothesized CBCL 1,5-5 scores will be computed. Even in a sub-sample of 500 toddlers we can estimate a correlation of 0.20 (or higher) with a power of 99% ( $\alpha = 0.05$ ; one sided testing). An even smaller sub-sample of 50 toddlers (of a small specific ethnic sub-group for instance) will allow to estimate a correlation of 0.40 with a power of 90% ( $\alpha=0.05$ ; one sided testing).

Based on the entire community sample ( $n=3.000$ ) the p90 of the BITSEA Problem Total Score of 2-year olds can be estimated with a precision of  $\pm 3\%$  for boys and girls separately.

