# INCLUSION SCHEDULE PER MONTH (21 MONTHS)

Validation of the brief Infant-Toddler Social and Emotional Assessment (BITSEA) and evaluation of the BITSEA as screening tool in Youth Health Care for preschool children

[name], MD,PhD, [name], MSc

|                                                                                                                          | 2009 |    |    |    |    |    |     | 2010 |     |     |     |     |     |     |     |     |     |     |     | 2011 |     |
|--------------------------------------------------------------------------------------------------------------------------|------|----|----|----|----|----|-----|------|-----|-----|-----|-----|-----|-----|-----|-----|-----|-----|-----|------|-----|
|                                                                                                                          | J    | J  | A  | S  | O  | N  | D   | J    | F   | M   | A   | M   | J   | J   | A   | S   | O   | N   | D   | J    | F   |
| Parents visiting preventive Youth Health Care Center with a child aged 24 months                                  |      |    |    |    |    |    |     |      |     |     |     |     |     |     |     |     |     |     |     |      |     |
| Inclusion of community sample (n= net 3000; 1500 intervention condition; 1500 control condition)                  | 5    | 10 | 20 | 40 | 60 | 80 | 100 | 125  | 160 | 200 | 200 | 200 | 200 | 200 | 200 | 200 | 200 | 200 | 200 | 200  | 200 |
| Parents referred to or visiting Youth Care (Jeugdzorg) or Youth Mental Health Care with a child aged 18-30 months |      |    |    |    |    |    |     |      |     |     |     |     |     |     |     |     |     |     |     |      |     |
| Inclusion of clinical sample (n= net 100)                                                                         | 1    | 2  | 3  | 4  | 5  | 5  | 5   | 5    | 5   | 5   | 5   | 5   | 5   | 5   | 5   | 5   | 6   | 6   | 6   | 6    | 6   |

|                                                                                                                                                                                                                                                       |
|-------------------------------------------------------------------------------------------------------------------------------------------------------------------------------------------------------------------------------------------------------|

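### The clinical validation sample can contain children referred partly on the BITSEA or KIPPPI-2 result at the 24-month visit, and children already in the community sample

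*Protocol*

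**What the plan says.** **Clinical sample.** Protocol 1.1 B takes net 100 children "that are circa 2 years old (18-30 months old) and that have been referred to Youth Care or Youth Mental Health Services", who "will be drawn through Youth Care/Mental Care agencies in the Rotterdam Rijnmond area". The inclusion schedule (Annex III) words the source slightly more broadly: "Parents referred to or visiting Youth Care (Jeugdzorg) or Youth Mental Health Care with a child aged 18-30 months". The parents complete the BITSEA, the KIPPPI-2 and the CBCL 1,5-5.

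**Community sample.** Protocol 1.1 A describes "A large community sample of 2-year olds (and their parents) in the Rotterdam Rijnmond region". The 30 teams recruit at the routine visit: "They will obtain informed consent from parents with 2-year olds eligible for the routine health assessment by preventive YHC at age 24 months". Annex III runs both samples over the same months, June 2009 to February 2011.

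**How referral arises.** Under Study Design, the YHC professionals "use the screening tools for emotional and behavioral problems, and decide on referral and follow-up care". Section 1.1 A says which tool feeds that judgment: "in the Intervention group the BITSEA will be used; in the Control group the KIPPPI-2". Section 2.2 adds that a 90th-percentile cut-off is used alongside the professional's other observations. The Introduction describes the KIPPPI-2 as usual care in the Rotterdam area.

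**Use of the data.** Section 1.4 builds the ROC curves with the clinical sample's results and names two criteria: (a) a clinical CBCL score and (b) referral to Youth Care or Child Mental Health Care. Norms and cut-offs come from the community sample. Section 1.5 adds the samples as if they were separate children: "A sample of 3.100 toddlers (3.000 of the community sample and 100 of the clinical sample".

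**The concern.** The age window extends six months either side of the 24-month screen, in the same region and months. A child aged 24 to 30 months who was referred after that visit meets the clinical criteria as written, and so does a child already enrolled in the community sample. Section 1.3 seems to expect such children: it lists the YHC professional's decision at the 24-month visit as a measure in the clinical sample where available.

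A child referred partly because the BITSEA was positive, and then used as a case to validate the BITSEA, introduces incorporation bias through sample entry. The same holds for the KIPPPI-2 and children referred by teams that use it. At stake are the AUC and sensitivity estimated against criterion (b), for both tools. Omitting Intervention-team professional findings from the community analysis would not cure this, because the selection lies in who enters the clinical sample. A child in both samples is also counted twice in the 3,100, and the two samples are then not independent.

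**Working it through.** **Inputs from the protocol.** Monthly inclusion (Annex III): community 5, 10, 20, 40, 60, 80, 100, 125, 160, then 12 × 200 = 3,000; clinical 1, 2, 3, 4, then 12 × 5 and 5 × 6 = 100. Teams (1.2): 28 + 14 + 7 + 3 = 52, of which 15 are Intervention. Births per year (1.2): 6,500 + 3,400 + 2,000 + 700 = 12,600, or 1,050 per month.

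**Assumptions, because the protocol gives no overlap rate.** Clinical recruits come from the regional pool in proportion, and their ages are even over 18 to 30 months.

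**1. The plan's own precision figure.** Hanley-McNeil: SE² = [A(1−A) + (n₁−1)(Q₁−A²) + (n₀−1)(Q₂−A²)] / (n₁n₀), with Q₁ = A/(2−A) and Q₂ = 2A²/(1+A). At A = 0.90, the half-width 1.96 × SE is:

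| Cases / non-cases | Half-width |
|---|---|
| 400 / 2,700 (10% of 3,000, plus 100) | 0.0205 |
| 310 / 2,790 (10% of 3,100) | 0.0232 |
| 100 / 3,000 (clinical cases only) | 0.0406 |

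The stated ±0.02 is reproduced with 310 to 400 cases, that is, with community cases included.

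**2. Clinical children who passed an Intervention-team visit first.** Applying the age assumption to the monthly schedule, about 47 of 100 recruits are past 24 months and had their visit within the study months.
- Upper figure, ignoring consent: 47.1 × 15/52 = 13.6, about 14.
- Lower figure, consenting community participants only: weighting each earlier visit month by that month's community inclusion / 1,050 gives 6.2 children screened first. Half are in the Intervention arm, about 3.

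For the KIPPPI-2, if all 37 other teams use it, the figure corresponding to 14 is 47.1 × 37/52 = 33.5.

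**3. Children in both samples.** Screened first 6.2, plus clinical first and later in the community sample 7.1, gives 13.3. A cruder figure with an assumed 90% reach is 3,000 / (12,600 × 21/12 × 0.9) = 3,000 / 19,845 = 15.1%. So about 13 to 15 of 100.

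**4. Effect on accuracy if every such child was selected by a positive BITSEA.** Binormal model with an assumed true AUC of 0.80: case mean √2 × 0.8416 = 1.190, and cut-off at the 90th percentile of non-cases = 1.282. Sensitivity is then 0.464, and cases above the cut-off have an AUC of 0.965 against non-cases. With a fraction f selected:
- AUC = (1−f) × 0.80 + f × 0.965: 0.805 at f = 0.03; 0.823 at f = 0.14.
- Sensitivity = (1−f) × 0.464 + f: 0.48 at f = 0.03; 0.54 at f = 0.14.

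**5. Precision.** Removing 14 duplicate cases (386 / 2,700) moves the half-width from 0.0205 to 0.0209.

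**The case against.** **The plan limits the exposure.** The clinical sample only adds to the validation. Criterion (a), the CBCL score, does not depend on referral. If clinical and community cases are pooled, 14 affected children among 400 cases are 3.5%. Referral also rests on other observations, not every referral after a visit follows from it, and a child who scored positive once may score lower on the repeat BITSEA. All this stands, and it makes the figures in step 4 upper bounds. It does not remove the problem for criterion (b) or for curves drawn from the clinical sample.

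**Counting each child once may be left to the SAP or data management.** This is fair for the analysis rule. Who may enter the clinical sample is an eligibility matter, and it is hard to repair later because the additional 24-month questionnaire is completed anonymously (1.2, 2.2). The Annex II overview is not available to check.

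**Stronger readings that the protocol does not support.**
- *The screening cut-offs are contaminated.* Section 1.4 takes norms and cut-offs from the community sample.
- *The bias favours the BITSEA over the KIPPPI-2.* Control teams refer with the KIPPPI-2, and it is usual care in the area. On the proportional model more children could be selected by the KIPPPI-2 (33.5 against 13.6), so the net direction is unknown and may be reversed.
- *Up to 15/52 = 29% of clinical children are affected.* This needs nearly all referrals to follow the visit, which conflicts with referrals spread evenly over the window.
- *Excluding only post-visit referrals from BITSEA teams would suffice.* Every post-visit referral left within the study period would then come from teams not using the BITSEA, chiefly KIPPPI-2 teams, in a sample that completes both tools.

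**Conclusion.** The point holds as a gap in the clinical sample's eligibility. As written, the tool that informed a referral can select some of its own validation cases, and a child can be in both samples. The likely distortion is upward, in the AUC and sensitivity of whichever tool informed the referral.

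The size is modest: about 3 to 14 of 100 clinical children with a prior Intervention-team visit, and an assumed AUC of 0.80 reading at most about 0.81 to 0.82. These figures rest on proportional sampling and even ages. Screening that itself prompts referral would raise the number of children; referral on other grounds and a lower repeat score would reduce the effect per child. Double enrolment (about 13 to 15 of 100) matters for independence between the samples, hardly for precision. The correction is worth making because it is cheap at enrolment and difficult afterwards.

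**What to change.** In 1.1 B, record for each clinical child the referral date, the referral source (including the YHC team) and whether a 24-month YHC visit preceded the referral. State that a child counts in only one of the two samples, and check this at enrolment.

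In 1.4, base the primary ROC and sensitivity estimates from the clinical sample on children referred before the 24-month visit, by the same rule for the BITSEA and the KIPPPI-2. If recruitment does not allow this, at least report both tools with and without post-visit referrals.

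**Cost.** A few extra chart items (a chart is already consulted for the diagnosis, though nothing says it names the YHC team), some matching work at enrolment, and fewer children in the primary clinical-sample estimate. With even ages, at most about half the 100 are past 24 months. If all of those were set aside, the formula in step 1 of the working gives a half-width of 0.057 with 50 cases and 3,000 non-cases, against 0.041 with 100. The real loss is smaller, because children recruited after 24 months but referred before the visit stay in.

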## Summary

The prevalence of psychosocial problems among preschool children is already high. Early detection and treatment of emotional and behavioral problems have a positive effect on prognosis. However, currently many cases are being missed. The Invent-group strongly suggested to implement and to evaluate the test properties and impact of the Brief Infant-Toddler Social and Emotional Assessment (BITSEA) for the purpose of screening of emotional and behavioral problems among very young children (1-3 year old). The BITSEA can be applied by preventive Youth Health Care in the Netherlands (YHC; 'Jeugdgezondheidszorg 0-4 jarigen'; 'Consultatiebureaus'). YHC has a reach of over 90% of parents/children during the preschool years. We propose to validate and to evaluate the impact of the use of the BITSEA as screening tool by YHC at the routine visit of parent/children at age 24 months. The study will be done by 30 YHC-teams in the larger Rotterdam area, including both metropolitan areas with extensive and varied non-Dutch communities and non-metropolitan areas representative of the Dutch population at large. The 30 YHC-teams will include a total of net 3.000 parents/children in the study; there will be a follow-up of 12 months after the YHC-visit at age 24 months. At random 15 YHC-teams will be assigned to apply the BITSEA as a new screening tool at age 24 months (Intervention condition). The other 15 YHC-teams will apply 'usual care', i.e. application of the KIPPPPI-'Consultatie Bureau Signalerings Instrument 2-jarige' (Control condition). In the Control group, parents will also complete the BITSEA (blinded for the YHC-professionals). The Child Behavior Checklist 1,5-5 (CBCL 1,5-5) (blinded for YHC) will be used to determine concurrent validity. Bilingual versions (Dutch; Turkish/ Arabic) will be offered. Additionally, a 'clinical' sample of (net) 100 circa 2-year olds (18-30 months old) referred to Youth Care and Youth Mental Health Services will be drawn through Youth Care/Mental Care agencies in the larger Rotterdam area. Parents of these children will also complete the BITSEA and KIPPPPI-2, next to the CBCL 1,5-5. Data from the 'clinical' sample will be used to add to the validation of the screening tools. The study consists of two parts. In Part 1, test properties of the BITSEA will be determined in 2-year olds. In Part 2, the use of the BITSEA as screening tool in 2-year olds will be evaluated in comparison with the use of the KIPPPPI-2. Data collection regarding the two parts of the study overlap. All 3.000 parents/toddlers in the study will complete the BITSEA and CBCL 1,5-5 at age 24 months, and at follow-up at age 36 months (in the Control group KIPPPPI-2 will be used for screening at age 24 months); (medical) charts and registers of care will be reviewed at follow-up. Test properties of BITSEA will be described according to current standards (Part 1 of the study). Multi-level analyses will be applied in evaluating the impact of the BITSEA compared to the KIPPPPI (Part 2 of the study).

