### ***1.4 Data analysis***

Test properties of the BITSEA will be described, including internal consistency, inter-rater reliability, factorial validity, concurrent validity with the CBCL 1,5-5, and discriminative validity (BITSEA results compared to professional findings). Receiver Operating Characteristic (ROC) curves for all possible cut-off points will be made available by using results of the ‘clinical’ sample. See Mackenbach et al (2008), page 240-253 for description of the test properties and procedures to evaluate the BITSEA as screening tool.

Two criteria will be used in this analysis: (a) a ‘clinical score’ on the CBCL 1,5-5; and (b) referral to Youth Care/Child Mental Health Care (and additionally other professional diagnoses by YHC-professionals or Youth Care/Mental Health Care professionals).

Normative data and cut-offs will be produced based on the total community sample. All test results will be explored and described for subgroups of children from ethnic minorities.

---

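### The clinical sample's entry rule is stated in two ways, neither requires a child emotional or behavioural problem, and criterion (b) counts referral itself as case status

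*Protocol*

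**What the plan says.** Three places in the protocol describe who enters the clinical sample of net 100.

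- Section 1.1 B: toddlers of 18-30 months "that have been referred to Youth Care or Youth Mental Health Services will be drawn through Youth Care/Mental Care agencies".
- Summary: children of the same age "referred to Youth Care and Youth Mental Health Services will be drawn through Youth Care/Mental Care agencies in the larger Rotterdam area". This agrees with 1.1 B.
- Annex III, inclusion schedule per month, row label: "Parents referred to or visiting Youth Care (Jeugdzorg) or Youth Mental Health Care with a child aged 18-30 months".

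Section 1.1 B adds that, with parental consent, "the diagnosis regarding the child will be retrieved from the (medical) chart". The parents also complete the BITSEA, KIPPPI-2 and CBCL 1,5-5.

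Section 1.4 states that ROC curves "for all possible cut-off points will be made available by using results of the" clinical sample, and names two criteria: a clinical score "on the CBCL 1,5-5; and (b) referral to Youth Care/Child Mental Health Care". Criterion (b) continues in parentheses: "and additionally other professional diagnoses by YHC-professionals or Youth Care/Mental Health Care professionals". Section 1.4 also says that norms and cut-offs come from the whole community sample.

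**The concern.** The Annex III label differs from 1.1 B and the Summary in two respects. It offers visiting as an alternative to referral, and it attaches the referral or visit to the parents rather than the child. Someone recruiting at an agency could follow either text.

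Neither text says what the referral must be for. The BITSEA is meant to detect internalizing and externalizing problems in the child, but a referral for any other reason satisfies both rules. Under criterion (b) that referral alone makes the child a case. The diagnoses are an addition and do not qualify the referral.

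A child without the target condition who correctly scores low on the BITSEA would then be entered as a false negative. Test properties are research question 1, and the clinical sample is the stated source of the ROC curves, so the meaning of a case under (b) should be clear.

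**Working it through.** **1. The plan's own precision figures.** Section 1.5 gives a 95% half-width of 0.02 for an AUC of about 0.90 with 3,100 toddlers (3,000 community, 100 clinical), and 0.08 for a sub-sample of 217. The Hanley-McNeil formula, with n1 cases and n0 non-cases, is

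SE² = [A(1-A) + (n1-1)(Q1-A²) + (n0-1)(Q2-A²)] / (n1·n0), where Q1 = A/(2-A) and Q2 = 2A²/(1+A).

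For A = 0.90: Q1-A² = 0.00818 and Q2-A² = 0.04263. The half-width is 1.96·SE.

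| Cases counted | n1 / n0 | Half-width, all 3,100 | Half-width, 217 |
|---|---|---|---|
| 10% of community plus all 100 clinical | 400 / 2,700 | 0.0205 | 0.078 (28 cases) |
| 10% of all 3,100 | 310 / 2,790 | 0.023 | 0.087 (22 cases) |
| The 100 clinical only | 100 / 3,000 | 0.041 | 0.154 (7 cases) |

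The 10% prevalence is stated in section 2.5 for Part 2; using it here is an assumption. Of these three readings, only the first returns both stated figures after rounding. That is consistent with all 100 clinical children being counted as cases, but it is an inference; section 1.5 does not say so.

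**2. Dilution alone.** Let f be the share of clinical children without an emotional or behavioural problem. The documents give no value for f. Suppose these children score like community non-cases (AUC 0.50) and the true AUC is 0.90.

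- Clinical children as the only cases: AUC = (1-f)·0.90 + f·0.50.
- Pooled with 300 community cases (10% of 3,000), the clinical share of cases is 100/400 = 0.25: AUC = 0.90 - 0.25·f·0.40.

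| f | Clinical only | Pooled, 400 cases |
|---|---|---|
| 10% | 0.86 | 0.89 |
| 20% | 0.82 | 0.88 |
| 30% | 0.78 | 0.87 |

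Each 10% costs 0.04 in the first setting and 0.01 in the second. Compared like for like, 0.04 is about one half-width of the clinical-only analysis (0.041), and 0.01 is about half the pooled half-width (0.0205).

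Sensitivity at 90% specificity, clinical only: the binormal separation for AUC 0.90 is 1.812, so sensitivity is Φ(1.812 - 1.282) = 0.702. With dilution it is (1-f)·0.702 + f·0.10 = 0.642, 0.582 and 0.521 for f = 10%, 20% and 30%.

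**3. Two things that weaken or reverse this.**

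- Referred children without a confirmed problem may still score above the community. With an elevation of 0.5 or 1 SD, the clinical-only AUC at f = 10% is 0.874 or 0.886 instead of 0.86.
- True clinical cases may be more severe than typical screening cases. An assumed shift of 0.5 SD gives Φ((1.812 + 0.5)/√2) = 0.949 at f = 0. At f = 10% it gives 0.9·0.949 + 0.1·0.5 = 0.904, and at f = 20% 0.859. At 10% the two effects roughly cancel.

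**The case against.** The strongest reply is that 1.1 B defines the population and Annex III only counts recruits by month. The community row of that table also has parents as its subject, probably because they complete the questionnaires. This has force: the label may be shorthand, and nothing shows that agencies would enrol families attending for unrelated reasons. Still, the label names two routes where 1.1 B names one, and the mismatch takes a line to remove.

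It can also be said that how referral and diagnosis combine under (b) belongs in an analysis plan, which is not shown. That is fair for the analysis detail. Who is enrolled and whether the referral reason is recorded are settled at recruitment.

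A reader might infer more than the documents support:

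- *That BITSEA accuracy will be understated.* Dilution pulls downward, but the share is unknown and a severer spectrum pulls the other way.
- *That non-cases count as cases throughout.* Criterion (a) classifies each child by CBCL score and does not depend on the referral reason. Chart diagnoses are retrieved too, so children without a diagnosed problem could be identified.
- *That cut-offs are distorted.* Section 1.4 bases them on the community sample, and section 2.2 has professionals use 90th percentiles of normative samples. The ROC curves are not said to select a cut-off.
- *That 10% dilution is twice the planned margin.* This sets the clinical-only shift of 0.04 against a margin of 0.02 that needs about 400 pooled cases.

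**Conclusion.** The point holds for criterion (b) only. The entry rule is worded inconsistently, no version asks for the target condition in the child, and referral for any reason is enough to be a case. The criterion (b) AUC and sensitivity would therefore mix detection of emotional and behavioural problems with detection of whatever else leads to referral.

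Under the dilution assumptions above, the loss per 10% of non-cases lies between about 0.01 (pooled) and 0.04 (clinical only) on an AUC of 0.90. The net direction cannot be determined from the documents. The clinical sample supplements the validation and takes no part in the Part 2 trial comparison, so this is an inexpensive improvement to Part 1 and no threat to the trial's main result.

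**What to change.** - Give section 1.1 B, the Summary and Annex III one child-based entry rule: the child has been referred. Align the visiting alternative in Annex III with that rule or remove it.
- Record the reason for referral. Section 1.3 already collects entries from the clinical child's record, but does not list the reason by name.
- In section 1.4, report the criterion (b) ROC twice: for all referred children, and restricted to those whose referral reason or chart diagnosis confirms an emotional or behavioural problem.

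The cost is protocol wording and one extra data item, since the chart diagnosis is already retrieved. The restricted analysis may have fewer than 100 cases. With 80 confirmed cases, for example, the formula above gives SE² = (0.09 + 79·0.00818 + 2,999·0.04263)/(80·3,000) = 0.000536, a half-width of 0.045 against 0.041 with 100. Restriction may also favour clearer cases and so flatter the instrument, which is why both analyses should be shown and neither should replace the other.
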